#### Indirect calorimetry.

Indirect calorimetry using a metabolic cart (MGC diagnostics) is performed on Day 2 of the baseline and plateau visits, and at the active weight loss visit. Participants are instructed to remain still with minimal movement and without sleeping and a fitted mask or canopy is placed securely over the nose and mouth to ensure that no gas escapes during the test. The participant rests for up to 30 minutes in a supine position to acclimate to the apparatus, then an approximate 20-minute test is performed to achieve steady state. Data from the indirect calorimetry are used to calculate respiratory quotient (RQ) and resting energy expenditure (REE).

#### Biopsies.

Adipose and muscle biopsies are conducted by qualified personnel on day two of the Baseline and Plateau visits and at the active weight loss visit. Following injection of local anesthetic, adipose biopsies are collected using negative pressure from an incision site located in the lower quadrant of the abdominal area, 10–12 cm from the umbilicus. To provide superficial anesthetic, up to 10 mL of 1% lidocaine is injected into the dermis of the target area. Once the anesthetic has taken effect and the site is sufficiently numb, a < 0.5 cm scalpel incision is made through the adipose tissue, and pressure is applied with gauze to stop bleeding. A biopsy needle is passed through the incision into the subcutaneous fat, and negative pressure is applied to obtain the sample. Pressure is applied to the incision with gauze while the sample is removed from the biopsy needle and placed on ice. The wound is then closed with steri-strips while the adipose biopsy sample is weighed and portioned into two cryovials, both of which are immediately flash frozen using liquid nitrogen then stored at −80°C until analysis.

Also under local anesthetic, muscle biopsies are collected via an incision over the vastus lateralis muscle, 8–10 cm proximal to the knee, lateral to midline, and medial to the IT band. To provide superficial anesthetic, up to 5 mL of 1% lidocaine is injected into the dermis of the target area. After the initial anesthetic injection, 1% lidocaine is again injected and advanced into the quadricep muscle, distributing the anesthetic into the muscle belly. Once the anesthetic has taken effect and the site is sufficiently numb, a number 11 blade scalpel is used to make an incision through the skin, subcutaneous tissue, fascia, and into the vastus lateralis muscle. A biopsy needle is inserted into the incision, through the fascial layer and is advanced an additional 2–3 cm past to ensure the biopsy needle is positioned completely within the muscle belly. Negative pressure is applied to obtain the sample, then pressure is applied to the incision with gauze while the sample is removed from the biopsy needle and placed on ice. The wound is then closed with steri-strips while the muscle biopsy sample is weighed and portioned into four cryovials; one cryovial is immediately flash frozen using liquid nitrogen and the remaining samples are transported on ice for processing and analysis.

### Measurement of Biospecimens

#### T-cell isolation and high-resolution respirometry.

Because peripheral blood mononuclear cells (PBMCs) represent a heterogeneous population of cells, T-cells are selected from freshly isolated PBMCs as previously described [61]. Three million cells are resuspended in supplemented DMEM (5 mM HEPES, 5 mM glucose, 1 mM sodium pyruvate, and 2 mM glutamate), and four million cells are resuspended in Mir05 (0.5 mM EGTA, 3 mM MgCl_2_, 60 mM lactobionic acid, 20 mM taurine, 10 KH_2_PO_4_, 20 mM HEPES, 110 mM D-sucrose). High resolution respirometry is performed using an Oroboros O2K respirometer (Oroboros Instruments, Austria) in intact cells (Protocol 1) and permeabilized cells (Protocol 2). For Protocol 1, T-cells are injected into chambers containing supplemented DMEM. Once basal respiration becames stable, leak respiration is induced with 1mM oligomycin, maximal uncoupled respiration is stimulated with consecutive titrations of 0.5 mM 2-(trifluoromethoxy) phenyl hydrazinylidene-propanedinitrile (FCCP), and complex III is inhibited with 2.5 μM antimycin A to induce non-mitochondrial respiration. For Protocol 2, T-cells are injected into chambers containing Mir05 supplemented with 1 μM of TMRM to measure membrane potential as previously described [61]. Cells are permeabilized with 4 μg/mL of digitonin. Leak respiration and maximal mitochondrial membrane potential is stimulated with 5 mM succinate, then 10 mM glutamate, 1 mM malate, and 5 mM pyruvate. Adenosine di-phosphate (ADP, 1 mM – 4 mM) is then titrated to induce oxidative phosphorylation. Maximal uncoupled respiration is then stimulated by sequential 0.5 mM FCCP injections. Complex I is inhibited with 0.5 mM rotenone, and Complex III with 2.5 mM antimycin A. Non-mitochondrial respiration under antimycin A is subtracted from all respiration rates for statistical analysis.

### Permeabilized muscle fiber preparation and high-resolution respirometry

A small piece (~15 mg) of fresh muscle tissue is immediately placed into ice-cold BIOPS (10 mM Ca-EGTA, 0.1 mM free calcium, 20 mM imidazole, 20 mM taurine, 50 mM K-MES, 0.5 mM dithiothreitol, 6.56 mM magnesium chloride, 5.77 mM sodium adenosine triphosphate, 15 mM phosphocreatine, pH 7.1). Tissue is manually teased with microdissection forceps into small fiber bundles of ~ 2 mg and permeabilized in ice-cold BIOPS with saponin (30 ug/mL) for 30 minutes and rinsed with BIOPS and Mir05 for 25 minutes. One fiber bundle is placed in a O2K chamber containing Mir05 supplemented with 25 mM blebbistatin. Protocol 3 includes a series of injections to induce respiration driven by oxidative phosphorylation of fatty acids, complex I and II substrates (Protocol 3: 4 mM ADP, 0.1 mM malate and 0.2 mM octanoyl-carnitine, 10 mM cytochrome C, 15 mM palmitoyl carnitine, 5 mM glutamate, 0.5 mM malate, 20 mM pyruvate, 10 mM succinate). Another fiber bundle is placed in a 2-mL O2K chamber containing Mir05 + blebbistatin and 10mM Amplex Ultra-Red reagent containing 5 U/mL superoxide dismutase and 1 U/mL horseradish peroxidase. Protocol 4 includes the addition of 10 mM succinate, 5 mM glutamate, 0.5 mM malate and 5 mM pyruvate to induce reverse electron transport and leak state. Adenosine di-phosphate (ADP) was then titrated to induce oxidative phosphorylation through a range of ADP concentrations (1 mM – 4 mM). Maximal uncoupled respiration is then stimulated by sequential 0.5 mM injections for protocols 3 and 4. Non-mitochondrial respiration under 2.5 μM antimycin A is subtracted from all respiration rates for statistical analysis. Oxygen is maintained at 500−200 mM uM.

#### Mitochondrial respiration in white adipose tissue (WAT) samples.

Approximately 100 mg of frozen WAT is used for the mitochondrial respiration assays. Samples are thawed on ice in mitochondrial assay solution (MAS), and the tissue is minced into smaller pieces with scissors. The fragments are collected and subsequently homogenized in ice-cold MAS. Mitochondria-enriched homogenates are obtained by differential centrifugation steps to remove the fat layer and other debris. Protein concentration is determined using the Pierce Rapid Gold BCA Protein Assay (Thermo Fisher Scientific).

Mitochondrial respiration in frozen samples is assessed using the Agilent Seahorse XFe24 Analyzer (Agilent Technologies, Santa Clara, CA) as previously described with minor modifications [62,63]. Homogenates containing mitochondria, and supplemented with cytochrome c, are loaded into Agilent Seahorse XF24 Cell Culture Microplates. For assessments of Complex I, II, and IV activities, substrates and inhibitors are injected subsequently as follows: NADH or Succinate + Rotenone (port A), rotenone + antimycin A (port B), TMPD + ascorbic acid (port C), and sodium azide (port D). Oxygen consumption rates are normalized to mitochondrial content.

### Retention/compliance/adherence

Adherence to the weight loss protocol is measured by attendance to behavioral weight loss program sessions (number of group and one-on-one sessions attended), dietary tracking (number of days per week the participant tracked >=500 kcal) and physical activity tracking (number of days the participants’ FitBit device was synced).

### Data management and availability

All participants are assigned a unique study ID upon enrollment, and all data is de-identified at the point of data collection. Data is directly electronically captured in RedCap when possible (e.g., questionnaires), otherwise data is entered into RedCap (e.g., clinical measurements) by study staff, or maintained on secure servers in its native form until processing (e.g., fMRI data) or integration into the study database. Data not directly captured is doubled data entered and checked for discrepancies. Data will be available from the study, once completed, upon reasonable request to the principal investigators. Required details and results will be reported to clinicaltrials.gov and further dissemination of results will occur through scientific conferences and publications.

### Statistical analysis plan

#### Aim 1.

Primary outcomes are oxidative phosphorylation and maximal respiratory capacity in T-cells, and permeabilized muscle fibers, the latter with fatty acid oxidation and complex I substrate. Secondary outcomes include T-cell and permeabilized muscle fibers uncoupling (proton leak respiration), adipose tissue mitochondrial respiratory capacity and coupling, UCP-1 expression, and inflammatory and lipolytic markers. As a prelude to inferential testing, linear regression will assess change in each measure as a function of potential confounding baseline covariates including % body fat, age, and sex as well as resting energy expenditure. Linear mixed models (adjusted for baseline confounders if needed) will be used to test for a main effect of time (baseline, active weight loss, plateau), followed by Bonferroni-adjusted formal *post hoc* testing to assess differences between phases and evaluate if a weight loss plateau represents a distinct metabolic state. We will then explore *evidence of cross talk* among T-cells, muscle, adipose tissue, and brain measures of appetite (See Aim 2 below). For measures that are changed from baseline by weight loss, we will perform linear regression amongst outcomes of the change from baseline to active weight loss or weight loss plateau. *Implications for weight maintenance* will be explored via linear regression of % weight change from plateau to 18 mo. as a function of the change in primary and secondary metabolic measures at plateau phase from baseline, adjusting for time between plateau and end of follow-up. Secondary analyses will use values measured at plateau (not change). Stratified analyses will assess sex as a biological variable. A sample size of N = 40 at active weight loss and plateau provides 99% power to detect within-subject differences between baseline and plateau and end of follow up for primary outcomes.

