Threshold regression modeling of individual percent weight loss trajectories is performed as an adjunct analytic strategy to the real-time approach and is used for interim and final classification of participants’ individual weight-loss phase at the time study visits were conducted. Threshold regression modeling is a statistical method that integrates the additional repeated measures of weights accumulated after an in-person study visit and takes full advantage of both pre- (real-time) and post-visit data to establish the trajectory and slope of weight loss at the time the visit occurred. It allows retrospective assignment of weight loss phase at the time of an in-person visit using all available data. For example, a participant who met weight loss plateau criteria by demonstrating minimal weight loss over a 21-day period might subsequently resume losing weight more rapidly. In this situation, interim threshold regression modeling would take the post-visit weight loss into account to determine that the participant was not, in fact, in a physiologic plateau at the time of the assessment. If the interim threshold regression modeling fails to confirm that the in-person plateau visit occurred during a study-defined plateau phase, monitoring for plateau study-criteria would resume, and if criteria are met on a second occasion, the participant would be invited for a supplemental in-person plateau visit. Upon completion of the entire 18-month study period, threshold regression modeling is also applied to individual percent weight loss trajectories for final assignment of study phase for all in-person study visits. Statistical analyses will use the final study phase assignments. See Fig 4C for representative example.

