#### Aim 2.

The primary analyses will evaluate differences between baseline and plateau phase in brain activation to visual food cues, specifically: 1) meal-induced change in mean extracted parameter estimates across all *a priori* satiety regions (high-calorie food vs. objects), 2) changes in pre-meal activation (high-calorie food vs. objects) from each of the four inhibitory control and reward modulation regions, and 3) associations of any findings with changes in Aim 1 metabolic outcomes. Outcomes for secondary analyses include mediobasal hypothalamic T2 relaxation time (vs. control regions) and meal-induced changes in salience network connectivity. Associations with weight regain post-plateau will be explored as will within-subject differences in regions outside *a priori* ROIs via fully adjusted voxel-wise comparisons. For within-subject comparisons, we will use linear mixed models that can accommodate repeated measures as well as missing data. Relationships between neurophysiologic measures and behavioral and hormonal correlates will be assessed using linear regression of change in behavioral correlates from baseline to plateau, as a function of each measure separately and together as covariates (i.e., changes in satiety response and inhibitory control activation), adjusting for time between plateau and baseline and, as needed, baseline covariates that are potential confounders such as sex, age, and % body fat. A sample size of N = 43 at plateau maintains 80% power to detect within subject differences in brain activation to visual food cues.

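### In the exploratory post-plateau weight analyses, post-visit weights help decide both who counts as being at plateau and the outcome value, which can bias the estimated associations

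*Protocol article*

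**What the plan says.** The section on remote weighing and real-time classification describes two ways of labelling a plateau. The real-time rule uses the slope over the preceding 21 days and triggers the visit. Threshold regression is then applied 1-2 months after the visit and again at study end, and it "takes full advantage of both pre- (real-time) and post-visit data". On the last step: "Upon completion of the entire 18-month study period, threshold regression modeling is also applied to individual percent weight loss trajectories for final assignment". The rule for analysis is general: "Statistical analyses will use the final study phase assignments".

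The worked example is a participant who stalls, is seen, and then resumes losing. The interim model "would take the post-visit weight loss into account to determine that the participant was not, in fact, in a physiologic plateau". Monitoring then resumes, and a supplemental plateau visit is offered if the criteria are met again. The plateau band is symmetric, within ±0.25 lb/week.

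Two planned analyses take weight after the plateau as the outcome. Aim 1 specifies "linear regression of % weight change from plateau to 18 mo. as a function of the change in primary and secondary metabolic measures", "adjusting for time between plateau and end of follow-up". Aim 2 states: "Associations with weight regain post-plateau will be explored". Neither is exempted from the final-assignment rule. Aim 3 does allow the real-time date as one definition of plateau entry, so the study already has a plateau definition based on pre-visit data.

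**The concern.** Using later weights to confirm a plateau is sensible when the question is whether a biopsy or scan was taken in a given phase. It is a problem when the later weights are themselves the outcome. A participant whose weight moves soon after the visit can lose the plateau label because of that movement, and the same movement is part of the change from plateau to 18 months. Membership of the sample then depends on the outcome.

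What is at stake is the estimated slope of later weight change on metabolic or brain change. This bears on the part of the overarching hypothesis that says plateau adaptations favour regain. Time between plateau and end of follow-up is the only adjustment stated for the Aim 1 regression. It corrects for unequal follow-up but does nothing about who was kept.

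**Working it through.** The article gives no figure for these analyses to reproduce. The Aim 1 power statement (N = 40, 99%) concerns within-subject change. The check is therefore structural first, then illustrative on assumed inputs.

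**Structure.** The label uses weights before and after the visit, up to 18 months. The outcome is weight change from plateau to 18 months. The two share the post-visit weights, and the general rule makes the label decide inclusion. No assumption is needed for this step.

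**Illustration 1: closed form, standardised slope.** Let X be the metabolic change, Y the later weight change and E the early post-visit trend. Assume joint normality, a true standardised slope ρ = 0.40, a correlation r between E and Y, and that E is related to X only through Y. Remove the fraction p with the lowest E.

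- With cut-point a and λ = φ(a)/(1 − p), the variance of E falls by k = λ² − aλ.
- The slope in the retained set is ρ(1 − kr²)/(1 − kr²ρ²).
- For p = 20%: a = −0.842, φ(a) = 0.280, λ = 0.280/0.80 = 0.350, k = 0.417.
- r = 1.0: 0.40 × 0.583/(1 − 0.417 × 0.16) = 0.233/0.933 = 0.25.
- r = 0.6: kr² = 0.150, so 0.40 × 0.850/(1 − 0.150 × 0.16) = 0.340/0.976 = 0.35.

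| Removed | k | Slope at r = 0.6 | Slope at r = 1.0 |
|---|---|---|---|
| 10% | 0.288 | 0.36 | 0.30 |
| 20% | 0.417 | 0.35 | 0.25 |
| 30% | 0.507 | 0.34 | 0.21 |

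The column r = 1.0 is an extreme, because it means selection on the outcome itself.

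**Illustration 2: one-sided versus two-sided removal.** Assumed inputs: outcome SD 5 percentage points, true correlation 0.30 (slope 5 × 0.30 = 1.50), r = 0.5 to 0.7, 400,000 simulated participants.

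- Removing only the 20-30% with the most early loss raises the mean by 0.9 to 1.7 points and cuts the slope to 1.15-1.36.
- Removing 15% in each tail leaves the mean unchanged and cuts the slope to 1.02-1.27.

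**Illustration 3: whole trajectories.** Weekly weights over 78 weeks at an assumed 240 lb, a three-week stall trigger, segmented regression with 0-3 breakpoints chosen by BIC, and confirmation if the fitted slope at the visit lies within ±0.25 lb/week. There were three scenarios of 1,200 triggered visits each. They differed in assumed mean post-plateau drift (0, 0.05 and 0.10 % per week).

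| Scenario | Confirmed | Confirmed by outcome tercile, low to high | Mean change, confirmed vs all | Slope, confirmed vs all |
|---|---|---|---|---|
| 1 | 1,024 | 0.86 / 0.90 / 0.80 | −0.23 vs −0.15 | 1.21 vs 1.29 |
| 2 | 1,012 | 0.87 / 0.88 / 0.78 | 1.01 vs 1.16 | 1.51 vs 1.41 |
| 3 | 1,024 | 0.90 / 0.86 / 0.80 | 3.07 vs 3.23 | 1.29 vs 1.33 |

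Confirmation varied with the outcome in every scenario. Of the unconfirmed visits, 43-50% lay on a loss slope and the rest on a gain slope. The mean did not move upwards. The slope was lower in two scenarios and higher in one, and these differences were small.

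**The case against.** A reader might infer from the worked example of resumed loss that the plan removes losers and so builds regain into the results. The documents do not support that. The example illustrates the rule and does not define it. The ±0.25 lb/week band is symmetric, so a visit on a gaining segment fails as well. In the trajectory simulation the confirmed mean was slightly lower than the mean of all visits. The planned Aim 1 analysis is also a regression, so a shift in the mean would move the intercept and not the association of interest.

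Other objections also have weight:

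- The model assigns phase from the slope at the time of the visit. Someone who holds steady and loses weight much later can keep the label. Selection therefore acts mainly through weights near the visit, and the r = 1.0 column is an outer limit.
- A participant not confirmed at interim can return through a supplemental visit, so removal need not be permanent. This softens the selection without curing it. For those who return, post-visit weights decided which visit counts and where the outcome starts. The article describes no replacement for a visit that loses its label only at the final assignment.
- Attenuation works against finding an association, so it does not favour the hypothesis. It would still make a null result hard to interpret.
- Both analyses are exploratory, and an article leaves much modelling detail to the full plan. However, the article does state which label the analyses use, without exception, and that stated rule causes the problem.

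**Conclusion.** The point holds in a limited form. Under the stated rule, post-visit weights help determine both inclusion and outcome in the Aim 1 weight-maintenance regression and the Aim 2 regain associations. The associations can be biased, most plausibly towards a weaker slope. That direction is clear when visits are removed on an early trend, from one tail or both, but was mixed in the trajectory simulation. The direction of any mean shift is not established.

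The size cannot be fixed from the document. It depends on the share of visits reclassified and on how closely early post-visit change tracks change to 18 months, neither of which is given. The reduction from 0.40 to 0.25-0.35 rests on an assumed one-sided removal of 20% and a correlation of 0.6 to 1.0.

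Severity is minor. No primary outcome, power statement or phase contrast is affected.

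**What to change.** Add an exception to the final-assignment rule for analyses whose outcome is weight after the plateau. Pre-specify that these associations are also estimated in all participants with a real-time-triggered first plateau visit, measured from that visit, whether or not it was later confirmed. That set is defined by pre-visit data only. Report it side by side with the threshold-confirmed set. State how many plateau visits were reclassified and whether they lay on a losing or a gaining slope. Base conclusions about weight maintenance on agreement between the two sets. Keep the final assignments for the phase contrasts.

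The cost is plan wording and one further run of each model, with no new data or visits. The real-time set will include some visits that the study's own method later judges not to be a physiologic plateau, which dilutes the plateau-specific exposure. For that reason the two sets should be shown together and neither should replace the other. Recruitment is expected to run to December 2026, so the wording can be settled before the final labels are complete.

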### Eligibility

Eligible participants are age 18–60 years, BMI 30–50 kg/m^2^, able to attend the study’s behavioral weight loss program classes and study clinic visits for phenotyping assessments, and living independently with the ability to prepare their own meals. Exclusion criteria include: current use of cigarettes or any nicotine products; use of cannabis; heavy alcohol use (≥ 2 drinks/d for women and ≥ 3 drinks/day for men); recreational drug use; known cognitive impairment; prevalent or prior history of stroke, Type 2 diabetes, bariatric surgery, eating disorder, or other medical conditions that could limit ability to participate; current pregnancy/6 months postpartum or breastfeeding (women only); current use of medications with appetite suppressive effects or current anti-coagulants; current participation in formal weight loss program; current or prior participation in research study involving weight loss; weight reduction ≥10% in the past year; food allergy, intolerance or unwillingness to consume study foods provided at functional magnetic resonance imaging (fMRI) assessment; MRI contraindications; and lack of technology needed to complete study activities. Following informed consent, participants undergo a non-fasting blood draw (hemoglobin A1c, metabolic panel, complete blood count, thyroid stimulating hormone) and height, weight and vital measurements, then complete questionnaires for final eligibility determination.

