#### Aim 3.

The primary outcomes of interest being explored in Aim 3 are entry into a weight loss plateau (Yes/No) and time from baseline (beginning of behavioral weight loss program) to plateau entry (continuous). Entry into a weight loss plateau will be defined as the 1) day at which a subject met weight loss plateau criteria during real-time monitoring or 2) first day of a weight loss plateau identified via threshold regression modeling at study completion. *A priori* predictors of interest for Aim 3 are based on available literature and our own findings and include the slope of the first active weight loss period [64]; trends over time in craving for carbohydrates/starches, dietary restraint, and disinhibition [65]; changes in T-cell and muscle maximal respiratory capacity; fasting ghrelin [66]; and baseline central satiety response, mediobasal hypothalamic T2 relaxation time [67], leptin [28] concentrations, and HOMA-IR [68]. Other predictors (i.e., inhibitory control) may be tested based on the findings of Aims 1 and 2; remaining predictors will be considered exploratory. Analyses will include only participants who achieved active weight loss. Fully adjusted models will include baseline or change in % body fat. Sensitivity analyses will be completed to evaluate whether excluding participants not achieving adherence will have the same or better predictive capabilities. A sample size of N = 40 participants who achieve active weight loss provides 91% power to detect effect sizes of R^2^ ≥ 0.36 at P < 0.05 for continuous outcomes.

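### Aim 1 assigns the assessment of sex to stratified analyses, which do not test whether the phase effect differs between women and men

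*Protocol article*

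**What the plan says.** All of this is in the protocol article, Statistical analysis plan, Aim 1.

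- On sex differences there is one sentence: "Stratified analyses will assess sex as a biological variable".
- The main analysis is a linear mixed model with phase (baseline, active weight loss, plateau) as a main effect, "followed by Bonferroni-adjusted formal *post hoc* testing to assess differences between phases".
- Sex also appears in a preliminary step that regresses change in each measure on "potential confounding baseline covariates including % body fat, age, and sex as well as resting energy expenditure". The mixed model is then adjusted for baseline confounders if needed.
- Power is stated for the pooled sample only: "A sample size of N = 40 at active weight loss and plateau provides 99% power to detect within-subject differences between baseline and plateau". Aim 1 gives no effect size, standard deviation or alpha.

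The article states no phase-by-sex term, no between-sex contrast labelled as the assessment of sex, and no rule for comparing the strata. The Eligibility section sets no sex quota, so the split is unknown.

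**The concern.** In Aim 1, to assess sex as a biological variable is to ask whether the change across phases differs between women and men. Separate models answer two other questions: is there a phase effect in women, and is there one in men? Neither result estimates the difference or gives its uncertainty.

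The strata are also smaller than the sample behind the power statement, and may be unequal. The sex with fewer participants is then the more likely to miss significance, even when its true effect is the same. A reader shown a significant phase effect in one sex only could take this for a biological difference when it reflects stratum size and chance.

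**Working it through.** **The plan's own figure.** The 99% power cannot be reproduced, because Aim 1 gives no effect size or alpha. It can be solved backwards. With a paired t-test (noncentral t), n = 40 and two-sided alpha 0.05, power is 99% at a standardised paired difference of dz = 0.695. The normal approximation is close: (1.960 + 2.326)/√40 = 0.678. Alpha is an assumption here. The article gives 0.05 only for Aim 3, where N = 40 "provides 91% power to detect effect sizes of R^2^ ≥ 0.36 at P < 0.05 for continuous outcomes".

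**Chance of significance in exactly one sex when the true effect is the same in both.** Let p1 and p2 be the paired t-test power in the two strata, with noncentrality dz × √n in each. Then

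P(exactly one significant) = p1(1 − p2) + p2(1 − p1).

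The sex splits are assumed. At dz = 0.695:

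| Split | p1 | p2 | Calculation | Result |
|---|---|---|---|---|
| 20/20 | 0.839 | 0.839 | 2 × 0.839 × 0.161 | 27% |
| 28/12 | 0.944 | 0.593 | 0.944 × 0.407 + 0.593 × 0.056 | 42% |
| 30/10 | 0.957 | 0.501 | 0.957 × 0.499 + 0.501 × 0.043 | 50% |

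A simulation of 100,000 runs per split gave 26.9%, 41.7% and 49.9%.

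**Sensitivity to the assumptions.**

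| Assumption | 20/20 | 28/12 | 30/10 |
|---|---|---|---|
| dz = 0.695, alpha 0.05 | 27% | 42% | 50% |
| dz = 0.776, alpha 0.0167 (99% power if Bonferroni over three contrasts) | 33% | 52% | 61% |
| dz = 0.8, alpha 0.05 | 14% | 29% | 39% |
| dz = 1.0, alpha 0.05 | 2% | 12% | 20% |

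With no phase effect in either sex the figure is 2 × 0.05 × 0.95 = 9.5%.

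**Direct test.** The baseline-to-plateau part of a phase-by-sex interaction was computed as a two-sample t-test on change scores. When the sexes do not differ it rejects in 5% of cases at any split (simulated 4.9% to 5.0%). For a true sex difference δ, in SDs of change, the noncentrality is δ/√(1/n1 + 1/n2). For δ = 0.695, as large as the whole phase effect:

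- 20/20: 0.695/0.316 = 2.20, power 57%
- 28/12: 0.695/0.345 = 2.01, power 50%
- 30/10: 0.695/0.365 = 1.90, power 46%

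For half that difference, power is 19%, 17% and 15%. The difference detectable with 80% power is 0.91, 0.99 and 1.05 SD of change.

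**The case against.** **The comparison is nearly in the plan already.** This is the strongest point on the other side, and most of it stands. The preliminary regression has change as its outcome, so its sex coefficient estimates the difference in change between women and men. With two time points and no other covariates, that is the phase-by-sex interaction. A reader might infer that the plan contains no between-sex comparison at all, and that would go too far. But the regression comes before inferential testing and its stated use is to find confounders. Adjusting the mixed model for sex as a main effect allows for a difference in level, not in change. The job of assessing sex is given to the strata.

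**No misuse is stated.** A reader might also infer that the investigators will declare a sex difference whenever one stratum is significant and the other is not. The article gives no such rule, and stratified analyses could mean sex-specific estimates with intervals. This stands: the percentages are the chance of discordant significance, not of a false claim.

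**The article is condensed.** The full plan may include an interaction, so its absence here is not the finding. The finding is that the method the article does name for this purpose does not answer the question.

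**The direct test is weak.** This stands too. It supports calling the interaction exploratory. It does not favour the strata, which give no interval for the sex difference and so do not show how imprecise the comparison is.

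**Conclusion.** The point holds as a limited one. The article names a method for assessing sex that does not estimate or test a difference between the sexes, and the one step that comes close has another purpose. If the strata were compared by significance, discordance without any true sex difference would arise in about 27% to 50% of cases over splits from 20/20 to 30/10. That rests on an effect of 0.695 back-solved from the 99% power, on two-sided alpha 0.05 and on assumed splits. At an effect of 1.0 it falls to 2% to 20%.

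The same criticism does not carry over to Aim 2, where the article mentions sex only as a possible covariate. The pooled primary phase test, its Bonferroni contrasts and the sample size are not affected.

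**What to change.** Add a phase-by-sex term to the planned Aim 1 mixed model. Base any statement about sex differences on the interaction estimate and its confidence interval, with the baseline-to-plateau component reported explicitly. Show sex-specific phase contrasts from the same model as description only, and say that significance in one sex alone will not be taken as evidence of a difference. Label the interaction exploratory and state its limited power.

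The cost is one model term and a sentence or two of text, with no new data. Recruitment is expected to run to December 2026 (protocol article, Recruitment), so the change can be made before the final analysis.
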